**Fig. 4 Fig4:**
[figure not shown]
Schedule of enrolment, interventions, and assessments. *Video laryngostroboscopy will also be carried out prior to consent to ensure that the participant is eligible for the study

### Protocol compliance

Protocol deviations, non-compliances, or breaches are departures from the approved protocol. The number of sessions of voice therapy offered and accepted will be individualised according to participant need. Therefore, there will be no required minimum number of voice therapy sessions attended overall in order to meet compliance. Participants will complete an online adherence questionnaire to assess their level of compliance with the home programme advised and to give information about treatment fidelity. Clinician compliance will be monitored by analysis of written clinical notes and video footage as outlined above.

Accidental protocol deviations can happen at any time. Any deviation must be adequately documented on the relevant forms and reported to the chief investigator and sponsor immediately. Deviations from the protocol which are found to frequently recur will require immediate action and could potentially be classified as a serious breach.

### Amendments

It is the sponsor’s responsibility to decide whether an amendment is substantial or non-substantial for the purposes of submission to the Research Ethics Committee (REC). If the sponsor wishes to make a substantial amendment, the sponsor must submit a valid amendment tool to the REC for consideration. Site research and development (R&D) departments will also need to be provided with information on the amendment in order to assess their continued capacity and capability. The Health Research Authority and site R&D departments will also be notified of non-substantial amendments with participating sites assessing whether the amendment affects the continued capacity for that site.

Any amendments (substantial or non-substantial) considered necessary by the study team will only be made after discussion with the R&D department of the sponsor. Approved amendments will be reflected in an update in the protocol version.

### Assessment of risk

The level of risk to participants in this trial is deemed low. Participants will be taking part in a therapy intervention based around indirect (education and advice) and direct (vocal exercises) therapy. Participants are given instructions to monitor and throat sensations and will be seen at regular intervals to discuss any symptoms. Some discomfort in the throat is anticipated post-operatively as patients will have surgery to the voice box. The surgical procedure does not form part of the study intervention.

Specific examples of symptoms which are expected to fluctuate during the course of the study include:Increased level of dysphonia (more hoarse, breathy, croaky) following surgeryIncreased sensory symptoms following surgery such as soreness and aching in the throat/neck

Participants are asked about their symptoms at each appointment. These are recorded and reviewed by the study team.

All adverse events or reactions will be reported to the chief investigator who will assess and document the severity of the event and follow written procedures, including escalating to the sponsor or discussion at trial steering committees, as appropriate.

Participants are also encouraged to report any concerns regarding the trial to the chief investigator. Contact details are on the PIS.

### Data management

All investigators and study site staff will comply with the requirements of the General Data Protection Regulation 2018 and Data Protection Act 2018 with regard to the collection, storage, processing, and disclosure of personal information and will uphold the Regulation’s/Act’s core principles. All information about participants will be handled in confidence and in accordance with Nottingham University Hospital’s Research Code of Conduct and Research Ethics and Caldicott principles. Case report forms (CRFs) will only collect the minimum required information for the purposes of the trial. CRFs will be held securely, in a locked room, or locked cupboard or cabinet. Access to the information will be limited to the trial staff and investigators and relevant regulatory authorities. Computer held data including the trial database will be held securely and password protected on the Nottingham University Hospitals NHS Trust network.

All participants will be given a study number on recruitment which will be used for all data analysis. An approved transcription service will transcribe interviews with participants and clinicians. All transcriptions will be pseudonymised for any names or places. Participants will provide optional consent to be contacted with a summary of the results after termination of the study. Specific pseudonymised data will be transferred to the University of Nottingham for analysis under the conditions of a Data Transfer Agreement.

Study specific data will be stored for a period of 5 years after the study has ended. Clinical assessment and therapeutic details and outcome data will be stored in accordance with the local NHS Trust’s policy.

### Criteria for terminating trial

The sponsor and funder reserve the right to temporarily suspend or discontinue this study at any time for failure to meet expected recruitment goals, for safety or any other administrative reason. The sponsor and funder shall take advice from the trial management group and trial steering group as appropriate in making this decision. Should the study be terminated, the research data will not be destroyed.

## Analysis plan

Analysis of quantitative data will be undertaken by the CDRF (AW) with support from the supervisory team (VB, PC, PL) and University of Nottingham medical statisticians if required.

Ongoing analysis throughout the trial will be undertaken to act as an early warning system to identify early problems with the primary feasibility outcomes including recruitment, retention, or data collection which may be able to be addressed and managed. Within trial monitoring, during monthly Trial Committee meetings and six monthly Trial Steering Committee meetings will consider whether attrition may be due to administrative processes which could be improved during the trial. We shall follow approved process for dealing with non-substantial and substantial amendments in this study. Any amendments (substantial or non-substantial) considered necessary by the study team will only be made after discussion with the Trial Steering Committee and Research and Innovation department of the sponsor at NUH. Approved amendments will be reflected in an update in the protocol version.

On study completion, descriptive statistics will be used to report the proportion of eligible patients recruited, the proportion of patients who complete the study, and the proportion of patients completing the intervention per protocol. Clinical outcomes, measured as degree of change between baseline and primary endpoint (6 months), will inform sample size calculations for a future definitive trial and consider whether the outcomes chosen are likely to show both statistically and clinically significant differences. The amount of missing data at each time point will be recorded to assess the feasibility of using each measure in a future effectiveness trial. SPSS [63] will be used to manage quantitative data and perform statistical analyses.

Qualitative analysis will be undertaken by the CDRF with support from the supervisory team. Analysis of interview data will be conducted using the framework technique, a type of thematic analysis, building on the work of Miles and Huberman [64]. The framework will be developed based on the COM-B model of behaviour change, considering barriers and facilitators to the intervention and research processes [65]. An appropriately trained PPI member will undertake secondary analysis of a proportion of the participant interview transcripts. Nvivo software will be used to facilitate stages of the data management and analysis process.

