## Background

Voice is a vital part of everyday human communication; however, one in three people will experience dysphonia in their lifetime [1]. The aetiology of dysphonia can be multifactorial, including muscle tension, tissue inflammation, nerve damage, or structural changes on the vocal folds [2]. Vocal fold cysts, polyps, papilloma, and Reinke’s oedema are examples of structural changes, termed ‘benign vocal fold lesions’ (BVFLs). BVFLs cause dysphonia by causing irregular vibration, preventing vocal fold closure, and increasing compensatory muscle tension [3, 4].

Voice loss because of BVFLs impacts individuals, society, and health resources. Individuals struggle to communicate on a daily basis and are unable to partake in hobbies, socialise, or fulfil caring responsibilities. Reduced activity and participation in society leads to increased rates of social isolation, anxiety, and depression [5, 6]. It is estimated that consequential time off work alone costs the UK £200 million each year [7] and direct healthcare costs in the US total £10–11 billion per year, making dysphonia comparable with COPD and diabetes [8, 9].

There are no clinical guidelines determining management for patients with BVFLs [10]. Patients may be offered surgery, pharmacological management, voice therapy, or a combination of approaches [11]. Pre-operative voice therapy can result in avoidance of surgery in up to 50% of patients with vocal fold polyps [10, 12–14]. Voice therapy may lead to lesion regression due to a reduction of phonotraumatic behaviours, improvement of throat symptoms as a result of improved voice care, or a reduction of muscle tension patterns. Emerging research suggests that voice therapy delivered by a specialist speech and language therapist (SLT) pre- and post-operatively gives greater improvement than surgery alone [15, 16]. However, it is unclear which elements of voice therapy are most effective, when they should be introduced or with which patients. In addition, treatment for individuals with BVFLs is influenced internationally by local capacity, historical practice, and surgeon preference [11, 17]. This can result in sub-optimal patient care [18], unnecessary surgery, additional hospital appointments, prolongation of symptoms [19], secondary complications from surgery [20], raised anxiety, and financial consequences [8].

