## Methods

### Study design

This is a multicentre, non-randomised, feasibility trial with an embedded process evaluation.

Problems associated with acceptability, compliance, delivery of the intervention, recruitment, retention, and effect sizes can occur if preparatory work is insufficient when evaluating the effectiveness in a definitive RCT [24]. The mixed methods design permits the depth of data collection and analysis required to inform changes in a definitive trial. The multicentre design will permit additional feasibility parameters to be gathered. This protocol follows guidance in the ‘CONSORT 2010 statement: Extension to randomised pilot and feasibility trials’ [31]. Process evaluation is an essential part of designing and testing complex interventions. Investigating the implementation of the intervention, including the fidelity, dose, adaptations, and reach, along with the context and mechanisms of impact informs interpretations of the outcomes of the trial. The Medical Research Council recommends including process evaluation at the feasibility stage, to understand and interpret feasibility findings and inform further development and evaluation stages [23, 32].

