### Secondary patient-centred outcomes

#### Schedule of data collection

Participants will attend 3 virtual or face to face research clinics. These will be scheduled at enrolment (pre-operatively), then at 3 and 6 months post-operatively to gather outcomes data. Participants will also be asked to complete a short adherence questionnaire online, or on paper according to patient preference. This will be sent to the participant when their therapist has confirmed completion of the PAPOV intervention. Participants who gave additional consent to be interviewed will be contacted 6 months post-surgery to talk about their experiences of the trial process and intervention acceptability. All clinicians who have been involved in delivering the intervention and who have given informed consent will also be contacted and interviewed (see Fig. 2).

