#### Clinical outcome measures

These outcome measures have been carefully selected to provide a multidimensional assessment of the voice, following a review of the current voice disorders literature, and discussion with patients and clinicians.

Patient-reported outcome measures.Voice Handicap Index-10 [36]: The VHI-10 is a validated patient-reported outcome measure covering physical, functional, and emotional aspects of voice. This is likely to be the primary outcome in a full trial. The VHI-10 is a shortened version of the VHI-30 [37], which makes it a quick and easy self-administered tool with no loss of utility of validity compared to the VHI. Scores can range from 0 (no handicap) to 40 (maximal handicap). A score greater than 11 is considered abnormal [38] and a change of 6 points over time represents a minimally important difference [39].Reflux Symptom Index (RSI) [40]: The RSI is a validated 9-point patient-completed questionnaire targeting symptoms associated with laryngopharyngeal reflux (LPR). The association between RSI and VHI improvement indicates good construct validity [40]. Basic science studies suggest that laryngopharyngeal reflux creates an environment that may predispose individuals to BVFLs because of changes in defence mechanisms of the vocal folds, cell to cell dehiscence, inflammatory reaction of the vocal folds, and reaction to phonotrauma [41] and is therefore of particular relevance to this patient group. Patients are asked to rate the severity with which they experience different symptoms on a scale of 0 (no problem) to 5 (severe problem). Scores can range from 0 to 45, with a score over 13 considered to be abnormal [42]. Information about pharmacological treatment for laryngopharyngeal reflux, including any changes in medication, will be gathered at research clinic to provide additional context for RSI scores.Vocal Tract Discomfort Scale (VTDS): The VTDS is a self-administrated questionnaire designed to measure the subjective perception of sensory discomfort in the throat (vocal tract) [43]. Although patients may report a change in voice quality, sensory symptoms are also frequently present [44]. There is a difference between the reported levels of discomfort depending on the cause of the voice problem. Patients with BVFLs were found to have higher scores on the VTDS than other types of voice disorders [44]. Therefore, it is of particular importance that these symptoms are monitored. The VTDS asks the patient to rate the frequency of occurrence and severity of eight subjectively different sensations: burning, tightness, dryness, aching, tickling, soreness, irritability, and lump in the throat. The frequency and severity are rated separately on a 7-point Likert scale ranging from 0 to 6 for frequency (0 = never, 2 = sometimes, 4 = often, 6 = always) and for severity (0 = none, 2 = mild, 4 = moderate, 6 = extreme). VTDS scores have been shown to correlate with the total scores of the VHI and decrease after voice training and vocal hygiene education in teachers [45]. A change in the Persian version of the VTDS of 6.0 points for each subscale following a therapeutic intervention has been interpreted as a real change with a 95% confidence level [46]; however, this is in patients with muscle tension dysphonia. Pre- and post-operative changes have not been studied to our knowledge.

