### Economic evaluation measures

Early involvement of economic evaluation is recommended by the Medical Research Council [23] and considered an essential component of feasibility testing by some [54]. One objective of feasibility studies is to define and refine methods for data collection [54]. This includes health economics data. Economic evaluation is necessary if implementation into standard care is anticipated. Although some attempts have been made to consider costs associated with dysphonia [8, 9], there is a lack of health economics data within the voice disorders literature, and certainly within the literature on management of BVFLs.Voice-Related Quality of Life [55]. The VR-QOL is a patient-reported, disease specific questionnaire for voice disorders. The 10-item questionnaire has been shown to be valid, reliable, and responsive to change in patients with dysphonia of varying aetiologies. Patients are asked to rate on a scale from 1 (none, not a problem) to 5 (problem is as ‘bad as it can be’) 10 statements about their voice over the previous 2 weeks. The inclusion of a disease specific quality of life measure to inform future measures of quality-adjusted life years (QALYs) is recommended [54].EQ-5D-5L [56]: The EQ-5D is a family of instruments to describe and value health. Patients are asked to rate five dimensions of health: mobility, self-care, usual activities, pain/discomfort, and anxiety/depression. The EQ-5D-5L was developed to improve sensitivity and to standardise language across the dimensions and gives patients five levels for each dimension rather than the previous three [56]. Evidence obtained from generic measures can be used to compare both the impact of health problems and the benefits offered by treatments across different patient populations and disease areas. Evaluation of the EQ-ED-5L can allow for a calculation of QALYs. Differences in scores can be used to show differences that may emerge in a future randomised controlled trial (RCT) [54]. It is unclear whether the EQ-5D-5L will be sensitive enough to show change in this population but as this has not been explored, it is important to understand whether this has potential value in a future trial.Voice costs questionnaire (VCC): The voice costs questionnaire is an unvalidated measure, developed by the authors in conjunction with patients with lived experience of voice disorders to capture the costs of living with a voice disorder and the associated treatment received. It has four sections: (1) impact on work, (2) hospital appointments, (3) medicines, and (4) other associated costs.

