## Discussion

This study will assess the feasibility of delivering a described voice therapy intervention protocol to patients who are undergoing surgery for removal of benign vocal fold lesions (BVFLs). Voice therapy effectiveness studies often suffer from a lack of explicit description of the intervention delivered, making it difficult to identify what components of the therapy may have contributed to the results reported. Considerable intervention development work has been undertaken, involving a wide range of stakeholders to ensure that this intervention is fully described. The intervention will be delivered by multiple therapists across two sites strengthening the research design and generalisability of findings. All people enrolled in this study will receive training in the PAPOV intervention. A limitation of this non-randomised approach is that the randomisation method for application in any subsequent RCT cannot be tested.

Feasibility will consider both trial processes and adherence to the intervention. The embedded process evaluation will enable deeper exploration of the factors contributing to the results obtained. Findings will inform the development and implementation of a subsequent effectiveness trial, should this be feasible.

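### The uncontrolled baseline-to-6-month change is named as an input to the definitive trial's sample size and outcome choice, but it cannot measure what therapy adds to surgery

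*Protocol article*

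**What the plan says.** The Analysis plan gives the clinical data two uses. The first is sample size: "Clinical outcomes, measured as degree of change between baseline and primary endpoint (6 months), will inform sample size calculations for a future definitive trial". The second, in the same sentence, is to "consider whether the outcomes chosen are likely to show both statistically and clinically significant differences".

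The rest of the article fixes what that change contains:

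- Study design: "This is a multicentre, non-randomised, feasibility trial with an embedded process evaluation".
- Discussion: "All people enrolled in this study will receive training in the PAPOV intervention".
- Schedule of data collection, on the research clinics: "These will be scheduled at enrolment (pre-operatively), then at 3 and 6 months post-operatively to gather outcomes data". Baseline is before the operation and the endpoint is after it.
- Assessment of risk: the operation is stated to lie outside the study intervention.

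The question of interest appears in the Background: "Emerging research suggests that voice therapy delivered by a specialist speech and language therapist (SLT) pre- and post-operatively gives greater improvement than surgery alone". Under Clinical outcome measures, the VHI-10 is named as the probable primary outcome of a full trial, and "a change of 6 points over time represents a minimally important difference". Under Economic evaluation measures, the EQ-5D-5L text reasons as the Analysis plan does: "Differences in scores can be used to show differences that may emerge in a future randomised controlled trial (RCT").

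The Discussion attributes one limitation to the non-randomised design, that the method of randomisation cannot be tried out. It does not mention that the change is uncontrolled.

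**The concern.** Informing a later effectiveness trial is the declared purpose of this study, so the quantity it hands on matters. The change within this single arm is the sum of at least four things: lesion removal, natural recovery, regression to the mean, and whatever therapy contributes. In a trial where both arms have surgery, the first three are largely shared and drop out of the comparison. What remains is the added effect of therapy, and a single-arm change says nothing about its size.

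The outcome-choice use has the same weakness, however the word inform is read. A measure that moves after a lesion is removed may still fail to distinguish two arms that both had the lesion removed. Judging measures on this change rewards responsiveness to surgery. At stake are a definitive trial that could be too small and an outcome set chosen on the wrong property.

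**Working it through.** **The plan's own figures.** Completers: 40 × (1 − 0.39) = 24.4, against the stated figure of more than 24. Time to recruit 20 at one site: 20 / (70 × 0.5 / 12) = 6.86 months, against the stated 7. Both reproduce. The article gives no alpha, power, SD, expected change or between-arm difference for a definitive trial, so there is no power-based figure to reproduce.

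**The relation that needs no SD.** For two means, n per arm = 2 × (SD × (z₁₋α/₂ + z₁₋β) / δ)². With the same SD, alpha and power, sizing on a change D when the true between-arm difference is d makes the trial too small by a factor (D / d)². For D = 12 this is (12/6)² = 4 when d = 6, and (12/3)² = 16 when d = 3. The 12 and the 3 are assumptions. The 6 is the article's VHI-10 value, borrowed here only as an illustration.

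**Illustrative numbers.** Assumed: VHI-10 SD of 6, 8 or 10, two-sided 5%, 90% power, 1:1 allocation, dropout ignored. For example, with SD 8 and δ = 12: 2 × (8 × 3.2415 / 12)² = 9.3, so 10 per arm.

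| Difference used for sizing | SD 6 | SD 8 | SD 10 |
|---|---|---|---|
| 12 | 6 | 10 | 15 |
| 6 | 22 | 38 | 59 |
| 4 | 48 | 85 | 132 |
| 3 | 85 | 150 | 234 |

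**Power lost if the change were used as the target.** With SD 8 and 10 per arm (sized on 12), the normal approximation gives power Φ(d / (SD × √(2/n)) − 1.96). For d = 6 this is Φ(6 / 3.578 − 1.96) = Φ(−0.283) = 39%. It is 20% for d = 4 and 13% for d = 3. Over assumed changes of 10 to 15 and SDs of 6 to 10, power is 25% to 52% for a true difference of 6, and 10% to 17% for 3.

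**Significance of the change as a guide to outcomes.** Assume 24 completers and an SD of change of 9. A paired t-test of a 6-point mean change then has about 88% power, and that figure is the same whether therapy contributed all of the 6 points or none.

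**What the data can supply.** Using the data for the SD alone would not cause the shortfall, but the SD would be imprecise. Its 95% interval runs from 0.82 to 1.28 times the estimate with 40 participants, and from 0.78 to 1.40 times with 24. The upper one-sided 80% limit with 24 is 1.16 times the estimate, which raises the required n by 1.16² = 1.35.

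**The case against.** The strongest reply is that the plan says only that the outcomes will inform the calculation. It never says the mean change will become the target difference. A change score also yields an SD, which a definitive trial can properly use. The article separately reports a 6-point VHI-10 value, and Sampling describes the study as estimating key parameters. Which statistic enters a future calculation is detail that an article may leave to a fuller document. This stands, and it makes the undersizing conditional.

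It does not dispose of the point. The sentence names the change as the input and mentions neither an SD nor a separately justified difference. The outcome-choice clause is a stated use of the wrong quantity, not an omission.

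Three further objections have force. A measure that does not move even across surgery is unlikely to separate arms, so responsiveness is a fair first screen. The definitive trial's control arm is nowhere defined: surgery alone is inferred from one Background sentence, and that section also describes variable care. The EQ-5D-5L sentence is hedged and rests on a citation. Finally, the progression criteria concern recruitment and attrition only, so no decision within this study depends on the sentence.

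**Conclusion.** The point holds in a limited form and should be fixed. The Analysis plan assigns an uncontrolled change to two tasks it cannot do: sizing a between-arm therapy effect, and showing that an outcome would separate arms that both have surgery. This conclusion needs only the single-arm design and the timing of the measurements. It assumes that both arms of the later trial would have surgery, as the Background suggests.

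The size of any shortfall is conditional on the mean change being used as the target difference: 4-fold for an assumed 12-point change against a true 6-point difference, and more if the true difference is smaller.

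A reader might infer that the plan will certainly produce an undersized trial. The text does not support that, because it is also compatible with carrying forward only the SD. A reader might also infer that almost every measure would pass a screen on significance. That is not supported either: the 88% figure is a single assumed VHI-10 scenario, the article itself doubts that the EQ-5D-5L is sensitive enough, and it says pre- to post-operative change on the Vocal Tract Discomfort Scale has not, to the authors' knowledge, been studied.

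**What to change.** 1. **Analysis plan, sample size.** Reword so that only three quantities are carried forward: the SD of the 6-month VHI-10, the baseline-to-6-month correlation, and the proportion with 6-month data. Give each a confidence interval, and use a cautious upper limit for the SD, for example the upper 80% limit.
2. **Target difference.** State that it will come from a separately justified between-group difference. The article's 6-point value describes a within-person change over time, so using it between groups needs its own justification.
3. **Mean change.** Report it with a 95% confidence interval as description only.
4. **Outcome choice.** Base it on completeness, acceptability and measurement properties, with responsiveness at most a first screen. Drop statistical significance of the uncontrolled change as a criterion.
5. **Discussion and Economic evaluation measures.** Add to the limitations that the single-arm change is not a treatment effect, and qualify the EQ-5D-5L sentence in the same way.

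The cost is wording only, with no new data and no change to conduct. The definitive trial may look larger and more expensive than a calculation based on the mean change would suggest.
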